#### Intervention description {11a}

##### Multi component family Intervention to Lower depression and Address Intimate Partner violence (MILAP):

The MILAP, summarized in Table 1 below, includes nine sessions delivered over nine weeks to young women aged 15–24, their husbands, and MILs.

All sessions will be delivered by counselors who have completed at least six months of psychosocial training and received specialized training to deliver MILAP from master’s-level psychologists and senior researchers. The sessions will take place in community-based counseling centers operated by either WOREC or local government, depending on participant convenience. MILAP is divided into three sections: MIL-DIL sessions, BCT sessions, and a triad summary session.

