##### Enhanced usual care (EUC):

EUC will be delivered by a separate team of counselors who have completed at least six months of psychosocial training but have not received specialized MILAP training, in order to avoid potential contamination. These counselors will conduct an initial safety assessment and offer: a) WOREC’s IPV rehabilitation services, which include access to a women’s shelter, safety and protection from the perpetrator, mental health counseling, legal support, and health services; b) educational materials on safety planning, the consequences of ongoing IPV, written resources for reducing IPV, and information about a nationwide IPV/DV hotline; c) referrals to wraparound services based on the woman’s needs and priorities, including legal support, safe housing, psychosocial counseling, health services, and livelihood support; d) referral to a one-stop IPV center, along with information about available options, including support for leaving the relationship if the participant expresses that desire.

Since this study includes women currently experiencing IPV, we will enhance the usual care by adding two key services: mental health crisis counseling and a referral pathway for those in need of specialized support.

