#### Participant timeline {13}

After the consent process is completed, we will conduct baseline assessments. This will be followed by the 1:1 random allocation of the recruited participants to either MILAP or EUC. Participants will then receive the intervention based on their allocation. We will conduct follow-up assessments at 1, 3 6, 9, and 12 months from baseline for all participants, regardless of intervention allocation. To evaluate the effectiveness of individual MILAP components, the one-month follow-up assessment will take place immediately after the completion of all MIL-DIL sessions and prior to the start of the BCT sessions. The three-month follow-up will be conducted after participants have completed all nine MILAP sessions. Figure 2 below shows the study timeline.

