### Data collection and management

#### Plans for assessment and collection of outcomes {18a}

We will use the REDCap platform to collect quantitative data. We will administer all assessment tools to both MILAP and EUC participants. We will administer demographic tool and prior adverse childhood experiences tool at baseline only. All other assessment tools will be administered at baseline and at follow-up time points: 1, 3, 6, 9, and 12 months post-baseline.

Depression will be measured using the widely used PHQ-9 tool, which is well-validated in Nepal.(70) We will use the IFVCS to measure abusive control, physical violence and sexual violence (77), and the PCL-C to measure PTSD.(83) Details of all outcomes measures, including demographic variables, are presented in Table 2.

To assess the mechanisms of change underlying MILAP’s effectiveness, we will collect qualitative data through serial in-depth interviews (IDIs) with all three members of the triad. We plan to conduct serial IDIs with approximately 15% of MILAP participants (n = 66), based on resource availability and the estimated number needed to reach thematic saturation (22 triads). We will conduct these serial IDIs at two timepoints: after the completion of MILAP and at the 12-month follow-up. We will purposively select triads to reflect variation in engagement with MILAP (e.g., across geographic areas and counselors), allowing us to capture a diverse range of intervention experiences. We will interview each participant separately using a semi-structured guide.

To conduct the cost-effectiveness analysis, we will collect data on the average costs per triad for delivering MILAP and EUC. We will also collect costs associated with each component of MILAP i.e. MIL-DIL, BCT, and the triad component. We will assess costs from a health system perspective, capturing both direct costs (e.g., staff time, training, materials, logistics) and indirect costs (e.g., monitoring, supervision, overhead, and administrative expenses) associated with implementation. In addition, we will capture costs incurred by participants and their households, including: (a) out-of-pocket expenses related to participation in the intervention (e.g., transportation and incidental costs), and (b) time costs, such as lost wages or productivity, due to time spent accessing and participating in the intervention.

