### Statistical methods

#### Statistical methods for primary and secondary outcomes {20a}

To evaluate the effectiveness of MILAP in reducing the proportion of women with moderate to severe depression and the levels of IPV and PTSD, we will conduct intention-to-treat (ITT) regression analyses at the end of the trial (12-month follow-up, single timepoint). Additionally, we will perform longitudinal analyses using a two-level regression model, incorporating an interaction between intervention arm and time, with repeated measures nested within participants (i.e., women) and a random intercept for participants. We will use logistic regression models for the binary outcomes (like depression defined by PHQ-9>9), and linear models for the continuous outcomes (like IFVCS score for IPV and PCL-C score for PTSD).

We will use thematic analysis to examine qualitative data from serial in-depth interviews (n = 66 across 22 triads). These interviews will help identify and prioritize potential mediators and moderators for quantitative analysis. We will triangulate the qualitative findings with quantitative data from the full cohort (n = 900 across 300 triads) and conduct a mixed-methods explanatory analysis to develop a comprehensive understanding of the mechanisms through which MILAP produces the intended outcomes and the relative contribution of each mechanism. To explore the mechanisms of change outlined in the conceptual model, we will conduct mediation analyses to assess whether, for example, the DIL-reported freedom of movement (FOM) score mediates the relation between intervention exposure and odds of DIL’s PHQ-9 >9. This will be examined by a structural equation model which simultaneously models the effect of the intervention on FOM (a), and of FOM (b) and intervention (c’) on depression, with a significant indirect effect (a*b) indicating mediation. (85) The model allows for continuous as well as categorical mediators and outcomes, and for multiple mediators to be included in the same model, to compare their relative impact.(86) We will use similar approach for other primary and secondary outcomes.

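### The additional longitudinal model assumes equal correlation between all six visits; if correlation decays or trajectories differ, its slope test and 12-month contrast are too liberal and its 1-month contrast too conservative

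*Protocol article*

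**What the plan says.** Section {20a} names two analyses. The first is "intention-to-treat (ITT) regression analyses at the end of the trial (12-month follow-up, single timepoint"). The second is introduced as an addition: "Additionally, we will perform longitudinal analyses using a two-level regression model, incorporating an interaction between intervention arm and time". The same sentence then gives its only random effect: "with repeated measures nested within participants (i.e., women) and a random intercept for participants". On the outcome type, the article says "We will use logistic regression models for the binary outcomes (like depression defined by PHQ-9>9), and linear models for the continuous outcomes". No random slope, serial correlation or robust variance is mentioned, and time is not said to be linear or categorical.

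Section {18a} sets the visits: "All other assessment tools will be administered at baseline and at follow-up time points: 1, 3, 6, 9, and 12 months post-baseline". That makes six unequally spaced occasions. Outcomes {12} defines both primary outcomes as change from baseline to 12 months, and Participant timeline {13} uses the 1-month visit to judge the MIL-DIL component separately.

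On delivery, Intervention description {11a} says "All sessions will be delivered by counselors who have completed at least six months of psychosocial training", and the comparator section says "EUC will be delivered by a separate team of counselors". Confidentiality {27} confirms that different counselors serve the two arms. The number of counselors is not given.

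**The concern.** With a linear outcome, a random intercept alone implies one common correlation for every pair of visits, whether one month or twelve months apart. On symptom and violence scores over a year, one would expect neighbouring visits to agree more closely than distant ones, and women to change at different rates. In either case the model pools short-gap and long-gap variability into one residual variance. It then understates the variance of long-range change and overstates that of short-range change. The arm-by-time term is a test of change, so this error goes straight into it. At stake are a false-positive rate above nominal for the sustained effect at 12 months and lost power at 1 month, where the MIL-DIL component is to be judged.

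A second, smaller issue is that women who share a counselor may have correlated outcomes. Counselors are nested in arm, and neither the 12-month nor the longitudinal model has a term for them.

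**Working it through.** **The plan's own figure.** Sample size {14} goes from 251 to 300 for about 15% attrition: 251/0.85 = 295.3, so 296, close to the stated 300. Evaluable women: 300 × 0.85 = 255, or 127.5 per arm. The article gives no visit-to-visit correlation, intraclass correlation, design effect or alpha. I assume two-sided 0.05.

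**Covariance: formula.** The visits are t = 0, 1, 3, 6, 9, 12 (mean 5.167, sum of squares about the mean 110.83). Let V be the true within-woman covariance and C the 6×6 centring matrix. With complete data, the random-intercept model's residual variance settles at s² = tr(CV)/5. For a contrast c that sums to zero, the model reports variance s²·c'c and the true variance is c'Vc. With VR = c'Vc/(s²·c'c), type I error = 2(1 − Φ(1.96/√VR)).

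**One case in full.** Assume total variance 1, made up of a stable part 0.3, a decaying part 0.4 (correlation 0.1 at 12 months, so 0.825 per month) and noise 0.3. The 0-to-12 correlation is 0.3 + 0.04 = 0.34, the 0-to-1 correlation is 0.3 + 0.4 × 0.825 = 0.63, and s² = 0.543.
- 12 months versus baseline: true 2(1 − 0.34) = 1.32; model 2 × 0.543 = 1.086; VR 1.22; type I error 7.5%.
- Linear slope: true 0.00799; model 0.543/110.83 = 0.00490; VR 1.63; type I error 12.5%.
- 1 month versus baseline: true 2(1 − 0.63) = 0.74; model 1.086; VR 0.68; type I error 1.8%.

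**Range over assumed structures (linear outcomes).**

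| True covariance (assumed) | Linear arm-by-time | 12-month vs baseline | 1-month vs baseline |
|---|---|---|---|
| Equal correlation | 5.0% | 5.0% | 5.0% |
| Random slopes adding 5-50% of baseline variance by month 12 | 5.7-11.3% | 5.4-8.6% | 4.8-3.6% |
| Stable part + decay + noise (0-to-12 correlation about 0.34-0.48) | 11-16% | 7.4-9.2% | 1.2-2.6% |
| Pure first-order decay, monthly correlation 0.90-0.98 | 24-28% | 13-16% | about 0% |

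The joint 5-degree-of-freedom interaction test stays at 5.0-5.7%, except under pure decay (8.7-9.5%).

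**Binary outcome.** A random-intercept logistic model with linear time was fitted to 500 simulated null trials per scenario (300 women, six visits). Type I error was 5.4% with constant correlation, 7.2% with random slopes and 8.4% with decay. The Monte Carlo standard error is √(0.05 × 0.95/500), about 1 percentage point.

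**Counselors.** Design effect DE = 1 + (m − 1) × ICC, with m = 127.5 divided by the number of counselors per arm. The standard error should be √DE times larger if both arms are clustered, and √((DE + 1)/2) times if only MILAP is.
- 10 per arm, ICC 0.01: m = 12.75, DE 1.12; factors 1.06 and 1.03; type I error 6.4% (both arms) and 5.7% (MILAP only).
- 4 per arm, ICC 0.05: m = 31.9, DE 2.54; factors 1.59 and 1.33; type I error 21.9% and 14.1%.

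**The case against.** The strongest reply is that this is the added analysis. The first-named analysis uses one timepoint and has no repeated-measures covariance, so the table does not apply to it. That stands: a reader might infer that the trial's main 12-month comparison is invalid, and the article does not support that. Only the counselor question reaches that analysis.

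A reader might also infer that the arm-by-time test is certain to be anticonservative, at around 25% or more. That does not follow either. There is no inflation under equal correlation. The highest figures need linear time, which the article does not state, and pure decay with no stable difference between women and no measurement noise, which is unlikely for self-report scales. The joint test is little affected in the other structures, and the logistic inflation is modest.

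On counselors, a reader might conclude that the standard errors are shown to be too small. The article gives no counselor number or intraclass correlation, and does not say that one counselor takes a triad through all sessions. Comparator care is partly a set of services and referrals. Clustering is therefore a possibility to check. At the expected 40% versus 10%, power would stay at about 98% with a design effect of 2.

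Finally, an analysis plan that is not shown could add robust variance or a richer covariance. That is fair, but the article does not leave the structure open: it states a random intercept for women in a two-level model, and it is that stated choice which is questioned.

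**Conclusion.** The point holds conditionally and for the additional longitudinal analysis only. The stated structure keeps its nominal level if all visits are equally correlated. If they are not, the slope test runs at about 6-16% and the 12-month contrast at about 5-9% under realistic assumed covariances, with upper limits of about 28% and 16% under pure first-order decay, and the 1-month contrast is conservative. These figures rest on assumed covariances, complete data and a two-sided 0.05 level.

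Counselor clustering is a separate question of unknown size that could touch both analyses. With 4-10 counselors per arm and an intraclass correlation of 0.01-0.05, both assumed, type I error would be about 6-14% if only MILAP is clustered and 6-22% if both arms are. That supports a sensitivity analysis, not a statement that the planned standard errors are wrong.

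**What to change.** - **IFVCS and PCL-C:** fit categorical visit, arm-by-visit and district, with an unstructured within-woman covariance and small-sample degrees of freedom, and take the 12-month contrast from that model. Either keep baseline as a response (six visits, 6 × 7/2 = 21 covariance parameters) or use it as a covariate (five follow-up visits, 5 × 6/2 = 15 parameters).
- **PHQ-9>9:** use a marginal logistic model with woman-level robust standard errors. Combine it with the multiple imputation already foreseen in section {20c}, because such a model otherwise needs stronger missing-data assumptions than a likelihood model.
- **Counselors:** record counselor ID at delivery. Add a sensitivity analysis of the 12-month and longitudinal results that allows for clustering: a counselor random effect in the linear models, and cluster-robust variance with a small-sample correction in the logistic model. Baseline precedes allocation, so in the longitudinal model the counselor effect should act on follow-up visits only.

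The cost is analysis-plan wording and one extra recorded field. Trial status gives March 2027 as the expected end of recruitment, so the ID can be captured as sessions are delivered; it may be hard to reconstruct later. The downside is somewhat wider intervals and few counselor-level degrees of freedom. Either covariance is readily estimated with about 300 women.

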#### Sample size {14}

Given the dual goals of the trial to assess MILAP’s effectiveness and understand mechanisms of action, sample size was determined for both mediation analyses and the impact on primary outcomes. Because mediation analysis is more statistically power-intensive, we calculated the sample size required to achieve 80% power to detect: a) the effect of the intervention on the primary outcome (the proportion of women with at least moderate depression), and b) a significant indirect effect of the intervention on depression, mediated by women’s FOM, one of the primary theorized mechanisms of change in our conceptual model. These calculations were based on the joint testing of both links in the hypothesized mechanistic pathway from intervention to FOM (link 1) and FOM to depression (link 2), using the approach of Vittinghoff and Neilands (78) and the corresponding medssp.R program. Based on our pilot study results, we expect the proportion of women with at least moderate depression (PHQ-9>9) post-intervention to be approximately 40% in the comparison group versus 5–10% in the intervention group. Based on the observed increase in FOM in the pilot study (65, 66), and to ensure clinical relevance, we specified a moderate effect of the intervention on the continuous FOM mediator, i.e., an R^2^ of 13% for FOM, per Cohen’s guidelines(79) for the first link, and an odds ratio of 0.5 per standard deviation (SD) of FOM for the dichotomous depression outcome for the second link of the indirect effect (i.e., a gain of 1 SD in FOM is associated with half the odds of scoring >9 on the PHQ-9). Assumptions for additional nuisance parameters that were necessary to be specified for this sample size calculation were: OR=0.77 for the direct effect of the intervention on depression (i.e., the remaining reduction in odds of PHQ-9 > 9 for the intervention group relative to EUC not mediated by FOM), and ρ_2_ = 0.30, a conventional moderate value (80) to account for correlation between the mediator and potential confounders. Given the 1:1 randomization, intervention exposure is 50% and it is reasonable to assume no confounding (ρ_1_ = 0) of the intervention-depression relationship. Based on these specifications, the required sample size was calculated to be n=251. To account for an anticipated attrition rate of approximately 15%, we determined an initial sample size of n=300 triads.

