### Assignment of interventions: Blinding

#### Who will be blinded {17a}

The study team member who will conduct assessment, i.e. assessment staff, will be blinded. Since MILAP is a behavioral intervention that is unique (involving woman, husband, and MIL), participants receiving the intervention cannot be blinded. In addition, research assistants will not be blinded, as they are for responsible for coordinating with participants and counselors to schedule MILAP sessions.

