**Table 1 T1:** 

Session Number	MILAP Session Type	Session Time	Focus	Participants
**1**	**MIL-DIL Sessions**	2 hours	Awareness of negative effects of IPV Discuss cultural norms and expectations Establish allyship	Woman and her MIL
**2**		2 hours	Gender empowerment Facilitate increased freedom of movement	
**3**		1 hour	Brief behavioral activation #1: list and plan rewarding activities	
**4**		1 hour	Brief behavioral activation #2: review experience + reinforce	
**5**	**Behavioral Couples Therapy (BCT) Sessions**	1 hour	Align on challenges, establish safety and trust Learn specific strategies to cope with stress	Couples: Woman and her Husband
**6**		1 hour	Revisit effectiveness of coping skills Understand and address communication challenges between partners	
**7**		1 hour	Activity to encourage caring behavior between partners Build communication skills	
**8**		1 hour	Active listening skills Review strategies to improve communication Addressing ongoing challenges, if necessary	
**9**	**Triad (Summary) Session**	1 hour	Review all lessons and prepare for long-term change	Woman, her husband and MIL

**Table 2: T2:** List of Key Variables and Measurement Tools

Screening Tools	Baseline	Follow-up (I, 3, 6, 9, and 12 month)
1. Screening Tool (W) International Violence Against Women Sumy (IVAWS) Patient Health Questionnaire-9: first 2 questions and 9^th^ question. If the score of PHQ-9 first 2 questions >3, then administer all PHQ-9 I f PHQ-9 trigger Q 9 is “More than half the days” or “Nearly every days”, then Administer 3 questions of Nepal Emergency Suicide Screener (NESS) Severity of Alcohol Dependence Questionnaire (SADQ)	1. Demographic Questions (W, H, MIL)	
	2. SRQS 21-item: Spousal relationship quality score (21 items) (W, H, MIL)	1. SQRS 21-item: Spousal quality relationship scale (21 items) (W, H, MIL)
	3. MILRQS 7-item: Mother-in-Law Relationship Quality Score (7 items) (W, H, MIL)	2. MILRQS 7-item: Mother-inLaw Relationship Quality Scale (7 items) (W, H, MIL)
	4. WAS 5-item: Women’s Autonomy Scale (4 items) (W, H, MIL)	3. WAS 5-item: Women’s Autonomy Scale measuring Freedom of Movement (4 items) (W, H, MIL)
	5. WHOQOL-BREF 9-item (psychological well-being and social functioning) (W)	4. WHOQOL-BREF 9-item (psychological well-being and social functioning) (W)

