2. Severity of Alcohol Dependence Questionnaire (SADQ) for Husband and MIL (H, MIL)	6. RSES 10-item: Rosenberg Self-Esteem Scale (10 items) (W)	5. RSES 10-item: Rosenberg Self-Esteem Scale (10 items) (W)
	7. FSS Fear Survey Schedule (focused on injury and sexual aggression fear) (W)	6. FSS: Fear Survey Schedule (focused on injury and sexual aggression fear) (W)
	8. ASI 16-rttm (Anxiety Sensitivity Index) (W)	7. ASI 16-item (Anxiety Sensitivity Index) (W)
	9. GAD-7: Generalized Anxiety Disorder-7 (W)	8. GAD-7: General ized Anxiety Disorder-7 (W)
	10. PHQ-9: Patient Health Questionnaire-9 & NEpal Suicide Screener (NESS) (W)	9. PHQ-9: Patient Health Questionnaire-9 & NESS (W)
	11. PCL-C 17-item: PTSD Checklist for DSM-4 (W)	10. PCL-C 17-item: PTSD Checklist for DSM-4 (W)
	12. BAD5–5F 9-ilem: Behavioral Actuation for Depression Scale - (9 items) (W)	11. BADS-SF 9-item: Behavioral Activation for Depression Scale - (9 items) (W)
	13. IFVCS 63-item: Indian Family Violence and Control Scale (63 items) (W)	12. IFVCS 63-item: Indian Family Violence and Control Scale (G3 items) (W)
	14. SRPS 8-item: Sexual relationship power scale (8 items) (W, H)	13. SRPS S-item. Sexual relationship power scale (8 items) (W, H)
	15. Adverse Childhood Experiences (W, H, MIL)	
	16. Additional 3 question from IVAWS on experiencing IPV to Mother-in-law (MIL)	
	17. GEMS 4-item: Gender Equality Men Scale (4 items) (W, H, MIL)	14. GEMS 4-item: Gender Equality Men Scale (4 items) (W, H, MIL)
	18. WHODAS 2.0 12-item: World Health Organization Disability Assessment Schedule 2.0 (12 items) (W)	15. WHOOAS 2.0 12-item: World Health Organization Disability Assessment Schedule 2.0 (12 items) (W)

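### The only mediation model stated takes freedom of movement and depression from the same unblinded woman, and a significant a*b is read as mediation without a check against the husband's and MIL's reports of the same scale

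*Protocol article*

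**What the plan says.** - **Model.** {20a} plans a structural equation model with paths arm to FOM (a), FOM to depression (b) and arm to depression (c'). Its one worked case, given as an example, asks whether "the DIL-reported freedom of movement (FOM) score mediates the relation between intervention exposure and odds of" PHQ-9 above 9 in the same woman.
- **Decision rule.** {20a} sets it as "with a significant indirect effect (a*b) indicating mediation".
- **Weight of the pathway.** {14} bases the sample size on an indirect effect "mediated by women’s FOM, one of the primary theorized mechanisms of change in our conceptual model".
- **Who reports what.** Table 2 lists "WAS 5-item: Women’s Autonomy Scale measuring Freedom of Movement (4 items) (W, H, MIL"), so all three triad members report FOM. Depression is "PHQ-9: Patient Health Questionnaire-9 & NESS (W"), the woman only.
- **When.** {18a}: "All other assessment tools will be administered at baseline and at follow-up time points: 1, 3, 6, 9, and 12 months post-baseline". FOM and PHQ-9 are therefore collected at the same visits. {20a} states no lag between mediator and outcome.
- **Blinding.** {17a} blinds assessment staff, but "participants receiving the intervention cannot be blinded". The MIL-DIL sessions promote FOM to the woman and her MIL.
- **Other reporters.** {20a} gives the husband's and MIL's FOM reports no stated role in the mediation model.

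**The concern.** Randomization protects path a from confounding. It does not protect path b, the association of FOM with depression within arms. When one person supplies both measures, low mood or a wish to give welcome answers can move both together. That error then sits inside path b, and covariates do not reliably remove it because it is part of the report itself. The ρ2 of 0.30 in {14} is a sample-size parameter and corrects no bias.

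At stake is Aim 2, the account of how MILAP works, and the evidence on FOM that the Discussion promises. The primary comparisons of depression and IPV between arms do not depend on this model.

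**Working it through.** **The plan's own figure.** {14} gives n = 251, raised to 300 for 15% attrition: 251 / 0.85 = 295.3, so 296, consistent with 300. A normal approximation to the joint test with the stated inputs gives about 101–108, not 251. That check had to assume two-sided alpha of 0.05 and a marginal prevalence of 0.225–0.25, and the cited program was not available. The mismatch is a separate matter. The present point concerns bias and does not rest on it.

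**Inputs from the protocol.** Completers: 300 × 0.85 = 255. Allocation 1:1. R² of 13% for arm on FOM. Depression 40% in EUC and 5–10% in MILAP (midpoint 7.5%). The mediation inputs in {14} imply a milder contrast:
- arm difference in FOM = 2 × √0.13 = 0.721 SD
- total OR = 0.5^0.721 × 0.77 = 0.607 × 0.77 = 0.467
- MILAP odds = (0.40/0.60) × 0.467 = 0.311, a proportion of 0.311/1.311 = 24%

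Both 40% vs 25% and 40% vs 7.5% were therefore run.

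**Assumed, not in the protocol.** The residual correlation between the woman's FOM report and her latent depression score: 0.10, 0.20, 0.30.

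**Check 1: real arm effect on FOM, no FOM effect on depression.** Within-arm SD of FOM is √0.87 = 0.933. The SE of the arm difference is 2 × 0.933/√255 = 0.117, so z is about 0.721/0.117 = 6.2. Path a is significant in practically every trial, and false mediation equals the false-positive rate of path b. Both links were tested at two-sided 5%, with a linear model for a and a logistic model for b given arm:

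| Residual correlation | 40% vs 25% | 40% vs 7.5% |
|---|---|---|
| 0.10 | 21% | 19% |
| 0.20 | 68% | 56% |
| 0.30 | 96% | 90% |

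Repeat runs gave 17–24%, 56–68% and 90–96% across the two columns. At 0.30 the spurious OR is about 0.56 per SD of FOM, close to the true OR of 0.5 that {14} plans on.

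**Check 2: no true arm effect on anything (n = 251).** A reporting tendency explains a share r of the variance in both reports and may shift in the MILAP arm.

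| r | FOM report shift | Joint test | Sobel test |
|---|---|---|---|
| 0.1–0.3 | none | 1–5% | 0–3% |
| 0.1 | 0.25 SD | 12% | 3% |
| 0.2 | 0.36 SD | 55% | 29% |
| 0.3 | 0.27 SD | 57% | 39% |
| 0.3 | 0.44 SD | 89% | 78% |

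With no arm shift, path b alone is falsely significant in 24–97% of runs, yet a*b rarely is. An arm difference in FOM, real or reported, is needed as well.

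**Check 3: what another informant buys.** This is the Check 1 set-up with the informant carrying 70% of the arm effect. With an informant error unrelated to the woman's depression score, false mediation is about 5%. With half the woman's residual correlation it is about 8–43%. With the same correlation the gain disappears (about 23% and 68% at 0.10 and 0.20, for 40% vs 25%).

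**Check 4: power for a true mechanism.** At OR 0.5 per SD, direct OR 0.77 and R² 13%, joint-test power is about 99% with FOM measured without error. With an informant who correlates 0.3, 0.5 or 0.7 (assumed) with true FOM within arm, it is about 26%, 59% and 87%.

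**The case against.** The best defence has four parts.

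- **The model is only an example in an exploratory analysis.** The next sentences of {20a} allow several mediators, and a condensed article may leave the choice of informant to the SAP. This stands in part: other reporters are not ruled out. But it is the only specification stated, it is the pathway that sizes the trial, the decision rule is explicit, and {20b} plans nothing beyond what is mentioned.
- **Aim 2 is mixed-methods.** {20a} triangulates with data from all 900 participants, and {18a} interviews the three members of 22 triads separately. This stands: the mechanism claim does not rest on one a*b. A reader might infer from the nesting of repeated measures within women that every stated model uses only women's data. That wording belongs to the longitudinal outcome model, not to the mediation analysis.
- **Mediator and outcome need not come from the same visit.** This stands. The tools are given at the same visits, but nothing stops an earlier FOM being paired with a later PHQ-9.
- **Husband and MIL are no neutral referees.** They are unblinded, the Background describes MILs as restricting daughters-in-law's movement, and household conflict can drive both FOM and depression. This stands, and Checks 3 and 4 show its size.

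**Conclusion.** The point holds in a limited form. As stated, the model cannot separate a FOM mechanism from shared reporting error in path b. If the arms also differ in FOM, really or in report, false mediation reaches about 20%, 60% and 90% or more at residual correlations of 0.10, 0.20 and 0.30. These correlations are assumptions; the protocol supplies none.

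Two stronger readings are tempting and not supported. One is that shared reporting bias alone produces a significant a*b: without an arm difference in FOM the joint test gives only 1–5%. The other is that another informant restores a 5% error rate, so that a mechanism claim should depend on that informant's result. The 5% rests on a residual correlation of zero, and such a condition could miss a true mechanism in most trials when informant agreement is low (power about 26% at a correlation of 0.3).

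What remains is a cheap improvement to the mechanism analysis, using data already planned for collection.

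**What to change.** In {20a}:

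1. Keep the woman-reported FOM model, and state which visit supplies the mediator and which the outcome.
2. Add as a prespecified sensitivity analysis the same mediation with husband-reported and MIL-reported FOM. Alternatively, use a latent FOM factor with the three reports as indicators, letting the error in the woman's FOM report correlate with her PHQ-9. The other two reports identify that correlation only if their own errors are unrelated to her PHQ-9; say so.
3. Report the results side by side. If the indirect effect appears only with the woman's report, describe FOM as a mechanism with caution. Do not make the other informants' result a condition for the claim.

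The cost is a few sentences and some extra modelling, with no new data. The husband's and MIL's reports are also unblinded, carry their own error, may share household causes with depression, and give lower power. The added analysis reduces the bias and does not remove it.
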